## Abstract

**Introduction:**

Current dietary assessment methods struggle to accurately capture individuals’ dietary habits. The ‘Standardised and Objective Dietary Intake Assessment Tool’ (SODIAT)-1 study aims to assess the effectiveness of three emerging technologies (urine and capillary blood biomarkers, wearable camera technology) and two online self-reporting dietary assessment tools to monitor dietary intake.

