^ While each tool has been used in nutrition research individually, it is their integration and collective use to enhance reporting accuracy that make this approach novel. The primary objective of the study is to calibrate the above dietary assessment technologies and tools for effectiveness to monitor exposure to foods/food groups commonly consumed in the UK in a controlled diet intervention. By conducting a comprehensive evaluation of their capabilities in accurately reporting dietary intake, the study aims to identify the most promising features of each technology. Subsequently, the research team will collaboratively integrate these features to create a combined optimal tool that maximises accuracy and usability which will be tested in future studies in the home environment (not described in this protocol).

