### Statistical analysis

Previous studies have shown that the misreporting rate of total energy expenditure between self-reported dietary assessment tools and double labelled water was 35 % with a standard deviation of 33 %.
^
37
^ To reduce the misreporting rate to <10%, an
*a priori* sample size calculation determined that to achieve a power of 80 % with a type 1 error of 5%, a total of 27 participants are required. This was increased to 30 participants to account for potential dropouts. Two separate clinical research centres were used, with both centres recruiting participants to ensure consistent demographics between sites (sex, age, and BMI).

The FFQ data collected at baseline will be used to describe cohort demographics and serve as a covariate in analysis to account for differences in habitual dietary patterns among participants. Additionally, the data from 4-day FFQ will provide average dietary intake data for the two study weeks, which can be combined with daily aggregated data, such as Intake24. This data will be compared with metabolomic data and images to assess consistency and identify any biases. Such comparisons are crucial for evaluating the alignment of self-reported dietary data with objective biomarkers.

Bootstrapped Lin’s concordance correlation coefficient (CCC) with 95% confidence intervals will be used to test the extent of agreement between each dietary assessment tool/technology and the nutrient composition of known diets and recorded compliance.

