### Primary and secondary outcomes to be measured

The primary outcome will be the accuracy of dietary reporting, measured at the end of each intervention week using the known quantities of consumed foods given to participants during the intervention days and dietary data collected from wearable cameras, spot urine samples, capillary blood samples, and self-reported dietary assessments.

Secondary outcome measures include: 1) the creation of a multiplatform model of dietary intake using g/day measured from wearable cameras and self-report dietary assessments, and μg/ml of dietary exposure biomarkers from spot urine samples and capillary blood samples at the end of the study, and 2) the design of a dietary intake study in a free-living population that will be informed by the results of the current dietary intake study protocol.

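### Lin's CCC against the known diet is planned for every tool, but as described the urine and blood biomarkers are not on an intake scale, so their coefficient would depend on the unit and could not be read as agreement

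*Protocol article*

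**What the plan says.** The Statistical analysis section of the protocol article plans "Bootstrapped Lin’s concordance correlation coefficient (CCC) with 95% confidence intervals", which "will be used to test the extent of agreement between each dietary assessment tool/technology and the nutrient composition of known diets", together with recorded compliance. It makes no exception for any tool. The Methods paragraph of the Abstract repeats the choice of CCC immediately after listing the urine and blood samples.

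The Abstract defines the tools as "three emerging technologies (urine and capillary blood biomarkers, wearable camera technology) and two online self-reporting dietary assessment tools". The primary outcome is accuracy of dietary reporting against the known quantities of food served, and its data sources include both spot urine and capillary blood.

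Units appear in the secondary outcome, the multiplatform model. It is to be built "using g/day measured from wearable cameras and self-report dietary assessments" and from "μg/ml of dietary exposure biomarkers from spot urine samples and capillary blood samples". The section on objective tools adds that urine is normalised by specific gravity, that a global dietary score is derived from the NMR profile, and that blood lipids are quantified against internal standards. The Introduction gives the primary objective as to "calibrate the above dietary assessment technologies and tools for effectiveness to monitor exposure to foods/food groups", without describing a calibration equation.

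**The concern.** CCC is a statement about y = x. It is reduced by weak correlation and also by any difference in mean or spread between the two measurements. That suits a tool that returns grams or nutrients, because a shift or a stretch is then misreporting. It does not suit a concentration or a score, where the difference in mean and spread from the reference carries no information about accuracy.

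Two of the three objective technologies are affected, in the primary outcome. A near-zero biomarker CCC could be read as a poor tool when it reflects only the unit. Set beside the CCCs for Intake24, eNutri and the camera, it could also mislead the choice of features to carry into the combined tool.

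**Working it through.** The article gives no expected or target CCC, so there is no figure of its own to reproduce on this point. The sample size of 27 concerns misreporting of energy and does not enter.

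**Step 1. Scales.**

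| Tool | Output described | Same scale as the known diet? |
|---|---|---|
| Camera | g/day | yes |
| Intake24, eNutri | g/day, nutrients | yes |
| Urine biomarkers | μg/ml, specific-gravity normalised | no |
| Urine NMR | diet-quality score | no |
| Capillary blood | lipids against internal standards; biomarkers in μg/ml | no |

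Specific-gravity normalisation corrects for dilution. It does not convert a concentration to intake.

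**Step 2. Formula.** CCC = 2·cov(x,y) / [var(x) + var(y) + (mean x − mean y)²]. For a marker exactly proportional to intake, y = kx with correlation 1 and k > 0:

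CCC = 2kV / [V + k²V + (1−k)²M²] ≤ 2k/(1+k²),

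where V and M are the variance and mean of the reference. The bound does not depend on V or M.

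**Step 3. Numbers from the article's own reference values.** Table 1 gives fibre of 21.8 and 38.8 g/d for the two diets. With equal numbers on each and full compliance (assumed), M = (21.8 + 38.8)/2 = 30.3, M² = 918.09, and V = ((38.8 − 21.8)/2)² = 72.25. The values of k are hypothetical, since the article gives no marker-to-intake ratio.

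| k | Correlation | Bound 2k/(1+k²) | CCC for fibre |
|---|---|---|---|
| 1 | 1 | 1 | 1 |
| 0.1 or 10 | 1 | 0.198 | 14.45/816.63 = 0.018 |
| 0.01 or 100 | 1 | 0.020 | 1.445/972.08 = 0.0015 |
| 0.001 or 1000 | 1 | 0.002 | 0.1445/988.50 = 0.00015 |

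The fractions are shown for the smaller k of each pair; the larger k gives the same value.

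**Step 4. A noisy marker.** In a simulation with 30 values per diet, assumed intakes around 40 and 160 g/d, slope 0.5 and correlation about 0.93, CCC was 0.51 in the starting unit. Multiplying the marker's unit by 1000 (μg/ml to ng/ml) gave 0.001, and dividing it by 1000 (to mg/ml) gave 0.0003. The correlation was unchanged.

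**Step 5. Two apparent repairs.** If both variables are standardised to equal mean and SD, CCC reduces to Pearson's r. If intake is regressed on the marker and predicted in the same participants, the predictions have variance r²V, covariance r²V with intake and the same mean, so CCC = 2r²/(1+r²). In both cases the bias component, which is the reason for choosing CCC, is removed by construction. The value is then not comparable with a CCC for Intake24 or the camera.

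**The case against.** The strongest reply is that nothing states that raw concentrations will enter the CCC. The μg/ml wording sits in the secondary outcome, the primary outcome names no unit, and the objective speaks of calibration. The article is condensed, the full protocol is deposited elsewhere and is not shown, and the article refers to previous intervention studies for the biomarker list and a previously validated NMR score. A conversion may therefore exist. This stands as far as it goes: a reader might infer that the team will certainly put μg/ml against g/day, and the text does not establish that. It does not remove the point, because the text assigns CCC to every tool without qualification and its only described model takes the biomarkers in μg/ml.

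Three stronger readings are also not supported.

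- **That no dose relation could be fitted because each food had one portion.** Many foods appear at one amount or not at all, but not all do. Summing the listed items over Diet 1 menus A and B and Diet 2 menus A and B, whole milk is 515 (200+25+40+250), 65 (25+40), 0 and 0 g, and wholemeal bread is 0, 0, 50 and 98 (44+54) g. Nutrient totals also differ between diets, for example saturated fat at 16.4 against 5.7 %TE. Dose information is limited, not absent.
- **That the main comparison of the study fails.** CCC stays usable for three of the five tools. No formal ranking is planned; the stated aim is to find and combine the most promising features.
- **That the coefficient is mathematically undefined.** The formula returns a number. That number cannot be interpreted as agreement.

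**Conclusion.** The concern holds in this form: a stated statistic does not fit two of the three objective technologies on the outputs described for them, and both are in the primary outcome. This is more than a detail left to an analysis plan, because the article fixes the method for all tools.

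The unit dependence follows from the formula and needs no assumption. The size in this trial cannot be computed, since the article gives no marker-to-intake scale; under the hypothetical values of k above, a perfect marker scores anywhere from about 0.00015 to 1. The conclusion assumes that no conversion to intake precedes the CCC. If one is specified in a document not shown, a statement to that effect would largely answer the point, provided the conversion was not fitted in the same participants it is judged on.

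**What to change.** 1. State that CCC applies only to outputs on the same scale as the reference: camera, Intake24, eNutri, and any biomarker-predicted intake that comes from an external calibration or from a model fitted in other participants.
2. For unconverted biomarkers, name the biomarker–food pairs in advance. Where the food differs between diets, use a within-person contrast or a discrimination measure (paired ratio, or AUC) with 95% CIs obtained at participant level. AUC also suits the NMR score as a measure of separation between the two diets.
3. A contrast of periods with and without the food is not available for items in both diets, such as tea, coffee, chicken, crisps and frozen mixed vegetables. For these use rank correlation, or change from the day-1 pre-diet sample expressed as a ratio. Rank correlation helps only where amounts vary: crisps are 25, 18, 25 and 0 g across the four menus, but tea is 245 or 240 g throughout, which leaves change from day 1.
4. State that these values are not to be compared directly with the CCCs of the intake-scale tools, and that dose information is limited because the menus are fixed and give few intake levels per food.

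The cost is rewording and modest extra programming; samples and data are unchanged. The price is that no single statistic covers all five tools. Because the article reports analysis as in progress, the change should be recorded and dated before biomarker results are compared with the diets.

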### Study diets

Participants consumed two controlled diets, one per study period, provided in a random order: Diet 1: non-compliant with UK dietary guidelines (e.g., high in saturated fat, free sugars, and salt and low in fibre); Diet 2: compliant with UK dietary guidelines, e.g., within the dietary reference values for saturated fat (≤10% total energy (TE)), free sugars (≤5 %TE), salt (≤6 g/d) and fibre (≥30 g/d) (
Table 1). The diets were matched for energy, protein, total fat and carbohydrate. Foods and drinks selected for each diet were selected to allow investigation of specific biomarkers.
^
21
^ Each diet consisted of a 2-day repeating menu (e.g., menu A served on days 1 and 3, and menu B served on days 2 and 4) as shown in
Tables 2 and
3. Bottled spring water was also be available to drink throughout the day. Meals and snacks were consumed at 2-hour intervals throughout the study days (9 am breakfast, 11 am morning snack, 1 pm lunch, 3 pm afternoon snack, and 5 pm dinner) and were served using identical tableware at each research unit (white crockery and clear glass on days 1 and 2 and patterned crockery and coloured glass on days 3 and 4); no foods/drinks were consumed directly from their packaging. Participants were also provided with a snack and bottled water to take home to consume before 8 pm and instructed not to eat or drink anything else before returning to the research unit the following day.

**Table 1. T1:** Nutrient composition of the study diets
*.

Nutrient	Diet A	Diet B
Energy (kcal/d)	2291	2168
Protein (%TE)	14.8	14.3
Total fat (%TE)	35.6	35.6
Saturated fat (%TE)	16.4	5.7
Carbohydrates (%TE)	46.8	43.5
Free sugars (%TE)	13.6	4.6
Dietary fibre (AOAC) (g/d)	21.8	38.8
Salt (g/d)	7.6	5.6

* Mean of menu 1 and menu 2 per study diet.

**Table 2. T2:** Study menus for diet 1.

Menu	Menu items and quantities

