### Study visit procedures

The day before starting each study period, participants were asked to restrict their caffeine and alcohol intakes and exercise levels to amounts that were usual for them and fast for 12 hours overnight (not consuming any food or drink, except water). Upon waking, participants also collected a first morning void (FMV) urine sample.

Participants attended the research unit at 8 am on day 1 (Monday) of each study period. Upon arrival, blood pressure, height and body weight were measured. A fasted capillary blood sample (OneDraw) was also self-collected and participants were set up with the wearable camera (which was worn continuously except if participants used bathroom) before being provided with breakfast. Habitual diet was recorded using the eNutri tool (4-week version). With the exception of mealtimes, participants had the rest of the day as free time but remained in the research unit. At the end of the study day (6 pm), participants were provided with bottled water and a snack for the evening, urine kits (for last evening void (LEV) and FMV samples) and a reminder checklist/log. Days 2-4 repeated day 1 except: 1) Intake24 was used on days 2-4 to record dietary intake during the previous 24 hours, 2) 4-day version eNutri was repeated at the end of day 4 (Thursday) to record dietary intake during the previous 4 days, and 3) capillary blood samples were not collected on day 3 (Wednesday). On day 5 (Friday), participants collected a final FMV, completed Intake24 and returned samples/equipment to the research unit.

Participants’ compliance to the study protocol was recorded by study investigators during the times when they were in the controlled environment. For the times spent outside the research unit, compliance was measured using sample/data collection records and self-reported deviations to study menus.

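### A weekly CCC against identical fixed menus mixes tool accuracy with the contrast between the two diets, and is least informative for energy

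*Protocol article*

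**What the plan says.** Under Statistical analysis, the article names one statistic for comparing tools with the truth: "Bootstrapped Lin’s concordance correlation coefficient (CCC) with 95% confidence intervals will be used" to assess "agreement between each dietary assessment tool/technology and the nutrient composition of known diets and recorded compliance". Under Primary and secondary outcomes, the primary outcome is accuracy of dietary reporting, assessed at the end of each intervention week against the "known quantities of consumed foods given to participants during the intervention days".

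Study diets fixes what that reference can be. "Each diet consisted of a 2-day repeating menu", and Tables 2 and 3 list one gram quantity per item with no scaling to the individual. The same section states: "The diets were matched for energy, protein, total fat and carbohydrate". Table 1 bears this out, with "Energy (kcal/d) 2291 2168" and "Total fat (%TE) 35.6 35.6" for the two diets.

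Recorded compliance also enters the reference. Under Study visit procedures, investigators record it on site, and outside the unit "compliance was measured using sample/data collection records and self-reported deviations to study menus". The article gives no size for these deviations.

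The sample size rests on a different quantity: energy misreporting of 35% (SD 33%), to be brought below 10%.

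**The concern.** CCC equals twice the covariance of tool and reference, divided by the sum of their variances plus the squared mean difference. It needs spread in the reference. A fully compliant participant's weekly reference takes one value per diet, shared with everyone else, so the pooled spread is set by how far apart the diets were designed to be. For the quantities matched on purpose, that spread is small or nil.

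Two readings of the results would then mislead. A low CCC for energy could be taken as poor reporting when the tool is good, and a high CCC for saturated fat could be taken as good reporting when the error is considerable. The Introduction says the results will identify the most promising features of each technology for a combined tool. If those features were chosen by comparing CCCs across nutrients, the choice would partly follow the menu design. CCC also does not estimate the misreporting percentage on which the sample size was based.

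**Working it through.** **The plan's own figure.** The difference is 35 − 10 = 25 points and the SD is 33. Then 2 × (33 × (1.960 + 0.842)/25)² = 27.35, close to the stated 27. This is a two-sample figure per arm, or equally a number of pairs with zero correlation. The number is not disputed here. What matters is that it concerns a mean difference in percent misreporting, not a CCC.

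**Inputs from Table 1** (its columns are headed Diet A and Diet B; which is which does not affect the CCC):
- energy 2291 and 2168 kcal/d
- protein 14.8 and 14.3 %TE
- total fat 35.6 and 35.6 %TE
- carbohydrate 46.8 and 43.5 %TE
- saturated fat 16.4 and 5.7 %TE
- free sugars 13.6 and 4.6 %TE

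**Assumptions, since the article gives no figures:** tool error CV; size of compliance deviations; 4, 9 and 3.75 kcal/g for converting protein, fat and carbohydrate to g/d.

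**Formula.** The reference takes values a and b equally often, so V = ((a − b)/2)² and m = (a + b)/2. For an unbiased tool whose error SD is cv × m, CCC = 2V / (2V + (cv × m)²).

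*Energy, cv 10%:* V = 61.5² = 3782 and (0.10 × 2229.5)² = 49,707, so CCC = 7564/(7564 + 49,707) = 0.13.

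*Saturated fat, cv 10%:* V = 5.35² = 28.62 and (0.10 × 11.05)² = 1.22, so CCC = 57.24/(57.24 + 1.22) = 0.98.

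*g/d values for the matched nutrients:* protein 14.8% × 2291/4 = 84.8 against 77.5; total fat 35.6% × 2291/9 = 90.6 against 85.8; carbohydrate 46.8% × 2291/3.75 = 285.9 against 251.5.

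| Quantity | CCC, cv 5% | cv 10% | cv 20% | cv 33% |
|---|---|---|---|---|
| Energy | 0.38 | 0.13 | 0.04 | 0.01 |
| Total fat, %TE / g/d | 0.00 / 0.38 | 0.00 / 0.13 | 0.00 / 0.04 | 0.00 / 0.01 |
| Protein, %TE / g/d | 0.19 / 0.62 | 0.06 / 0.29 | 0.02 / 0.09 | 0.01 / 0.04 |
| Carbohydrate, %TE / g/d | 0.52 / 0.77 | 0.21 / 0.45 | 0.06 / 0.17 | 0.02 / 0.07 |
| Saturated fat, %TE | 0.995 | 0.98 | 0.92 | 0.81 |
| Free sugars, %TE | 0.995 | 0.98 | 0.92 | 0.82 |

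A tool with 5% error on energy (0.38) thus scores well below a tool with 33% error on saturated fat (0.81). In a simulation of 30 participants on both diets at cv 20%, the 95% range of the CCC was −0.03 to 0.10 for energy and 0.89 to 0.95 for saturated fat.

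**Within one diet**, at weekly level with full compliance, the reference is constant. The covariance is 0, so CCC is 0 for any tool with some error, whatever its size.

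**Allowing for compliance.** If recorded deviations give the reference a within-diet CV of c, V becomes ((a − b)/2)² + (c × m)². For energy at cv 10%:
- c = 5%: V = 3782 + 12,427 = 16,209, so CCC = 32,418/(32,418 + 49,707) = 0.39.
- c = 10%: V = 3782 + 49,707 = 53,489, so CCC = 106,978/(106,978 + 49,707) = 0.68.

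At cv 20%, energy is 0.06, 0.14 and 0.35 for c = 2%, 5% and 10%, while saturated fat stays at 0.92 throughout.

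**Does CCC still respond to accuracy?** For one nutrient, yes. Saturated fat falls through 0.98, 0.92, 0.81 and 0.65 as cv rises through 10, 20, 33 and 50%.

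**The case against.** The strongest case against has four parts.

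**CCC still measures accuracy in part.** For a fixed nutrient and common reference it falls with both bias and random error, so it can order the tools, and comparing tools is what the study is for. This stands. A reader might infer that the planned CCC reflects only the diet contrast and says nothing about the tool; the saturated fat series contradicts that. The article also does not say that CCCs will be compared across nutrients, so that is a risk of interpretation, not a planned step.

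**Units matter.** The zero for total fat comes from Table 1's % of energy. The tools report amounts, and in g/d the figure is 0.13. This also stands, but the g/d values for the matched nutrients remain low.

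**The level of analysis is open.** The statistical section does not say day or week, pooled or per diet, nutrient or food item. Menus A and B would add spread at day level; how much cannot be computed, because Table 1 gives only their mean. At item level (Diet 1, Menu A, error proportional to item weight), CCC within a single diet is about 0.99 at 10% error. So the zero within a diet is conditional and cannot be stated for every possible analysis. However, the outcome section sets the week as the time point, and the 4-day FFQ covers the whole study period in one report.

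**Recorded compliance adds variation.** This is true, and with large deviations the energy CCC could be moderate. The coefficient would then depend on how far participants strayed from the menus, which is not tool accuracy either.

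The article also plans to compare self-report with metabolomic data and images to look for bias. That is useful, but it compares tools with one another, not with known intake.

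**Conclusion.** The point holds in a limited form. At the weekly level named for the primary outcome, CCC against known intake confounds tool accuracy with the designed diet contrast. At the same assumed 10% unbiased error and full compliance, it is about 0.13 for energy, 0.13 to 0.45 for total fat, protein and carbohydrate in g/d, and about 0.98 for saturated fat and free sugars. A 5% compliance CV lifts energy only to 0.39; a 10% CV would lift it to 0.68. The values therefore cannot be read as absolute accuracy or compared across nutrients. They say least about the matched quantities, which include energy, the basis of the sample size.

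The documents do not support the stronger conclusions that CCC is uninformative for every nutrient, that it is zero under any level of analysis, or that the trial cannot measure accuracy. The data for a direct measure are being collected; what needs changing is the choice of main statistic. All CCC values here rest on assumed error and compliance CVs.

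**What to change.** In Statistical analysis, add as the main accuracy measure the percent difference between tool and known intake, per participant and per diet, with known intake adjusted for recorded compliance. Apply it to the tools that output intake amounts. For each nutrient and food group, report mean bias with a confidence interval, 95% limits of agreement and the share within ±10%, allowing for repeated measures on the same participant. This is on the same scale as the misreporting target behind the sample size.

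Keep CCC as a supporting measure for components that differ between the diets. State its level (day or week, pooled or per diet) and units, and say that its value depends on the diet contrast and should not be compared across nutrients.

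The cost is small: the same data, no new procedures, slightly more analysis, and the loss of a single headline coefficient. Since Study status reports analysis in progress, the change should be dated and should record whether any comparison with known intake had already been seen.
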